### Blinding

The participants will be in cardiac arrest at the time of their enrollment and at the time of performance of the intervention; they will not be aware of the arm of randomization to which they are initially assigned and will be informed as soon as their clinical status allows it.

The study does not involve a blind setting for the healthcare providers, but outcome assessors and data analysts will be blinded to allocation groups C or D. Data are automatically blinded by the system when they are entered in the online electronic case report form (eCRF). The blinding is not completely possible for groups A and B because the length of the CPR relay differs between the 2 groups and is visible on the data regardless of the allocation masking.

### Randomization, allocation

The block randomization, stratified by trial centers, is performed using a randomization list from a centralized secure online server (internet) 24/7. A backup solution with sealed opaque envelopes will be available in each vehicle participating in the study for situations that do not allow access to the secure randomization server (off-grid area, connection difficulty). There is a stratification of the draw at each center in a 1:1:1:1 distribution: (A + C) 2 min blind, (A + D) 2 min with guidance, (B + C) 4 min blind, and (B + D) 4 min with guidance (Fig. 1).

### Device description

The CPRmeter^®^ is a CC guidance device marketed by Laerdal (LAERDAL Medical France, Limonest, France) that provides real-time feedback on CC. The CPRmeter^®^ is placed under the hands of the CC provider on the patient’s chest, where it is secured with a disposable adhesive (Fig. 2). The dimensions of the CPRmeter^®^ are 154 mm × 64 mm × 28 mm, and it weighs 227 g. Feedback data are provided to the user via a 26 mm × 26 mm color screen located above a 100 mm × 55 mm rubber surface for the positioning of the rescuer’s hands. It provides visual feedback to guide the depth, release, and frequency of the CC (Fig. 3). The hand position is represented on the left part of the screen by a white cursor going up and down on a scale according to the CC. Green targets at the top and bottom of the scale illuminate when they are reached by the cursor. In the case of insufficient depth or release CC, yellow arrows appear to indicate the CC modification needed. The CC frequency is shown on the right side of the screen by a needle on a speedometer with a green target area in the middle that illuminates when reached by the needle. The target values are defined by the manufacturer (Laerdal^®^) according to the 2015 recommendations, in effect when the device was designed [9]. The indications provided by the CPRmeter^®^ are visual only and not audio. All data are automatically recorded in real time on the internal memory of the device.

**Fig. 2 Fig2:**
[figure not shown]
Position and use of CPRmeter^®^ during external chest compression

**Fig. 3 Fig3:**
[figure not shown]
CPRmeter^®^ screen display and feedback provided during external chest compression

The implementation of the device will be done in collaboration with the Laerdal^®^ Company, which will provide theoretical and practical initial training of investigative teams on the use of CPRmeter^®^ and data recovery before the start of the trial. The presentation and training for the use of the device will be of sufficient duration, and the mastery of the device will be ensured.

### Trial interventions

CA, matching the eligible criteria, managed by an out-of-hospital resuscitation team can be included according to a procedure of immediate vital emergency (article L1122-1-3 of the Code of Public Health) [27]. The randomization is performed by the out-of-hospital resuscitation team’s doctor during the transportation on the spot to know the randomization arm before the arrival at the place of the intervention. The patient is randomized using the online centralized 24/7 server or the backup sealed opaque “off-grid area” emergency randomization envelopes as described in the “Randomization, allocation” section above.

For all groups, the CPRmeter^®^ CC guidance system was positioned on the patient’s chest with a disposable adhesive. The CPRmeter^®^ is always on for all groups. (1) In the CC guidance situation by the CPRmeter^®^ (group D), rescuers have onscreen real-time visual feedback on the quality of the CC performed and indications of corrections to improve the quality, if necessary. (2) In cases of nonguidance of the CC by the CPRmeter^®^ (blind), a specific screen cap is set up on the screen to hide the feedback in the unguided group (group C). The CPRmeter^®^ is always on to record the CC quality data.

The duration or rhythm of a relay is the time during which a rescuer performs a CC before being relayed by another rescuer. This time is 2 min in group A according to the guidelines in effect and 4 min in group B, which is the experimental group.

The CPR of OHCA is therefore normally undertaken according to the guidelines in effect by the out-of-hospital resuscitation team, except for the relay rhythm in group B, which is 4 min. Due to the 2 × 2 factorial design, four situations are possible (Fig. 1):
CC unguided + relay between 2 rescuers switching at 2 min (C + A)CC unguided + relay between 2 rescuers switching at 4 min (C + B)CC guided + relay between 2 rescuers switching at 2 min (D + A)CC guided + relay between 2 rescuers switching at 4 min (D + B)

Apart from the guidance or blinding of the CC and the duration of the CC relays, the resuscitation is similar to the usual practice of the out-of-hospital resuscitation team and complies with the guidelines in effect [9]. In case of use in relay of the CC of an automated CC device, the patient remains included in the study, the CPRmeter^®^ data (main judgment criteria) are retained, but no more data (secondary criteria) are collected after the implementation of the automated CC device (no blood sampling or CPC score).

Low-flow time is the time during which a CC is performed, generating a minimum cardiac output toward the organs. The no-flow time is the time during which no CC is performed. There is therefore no organ perfusion generated. The no-flow and low-flow times are complementary, and their sum is the patient’s management time. The CCF is the percentage of time during which the patient receives CC over the entire time of rescue (CCF = low-flow time/total time). CC quality data (depth, release, and frequency) as well as time with CC (low-flow) and no CC (no-flow) are automatically collected by the CPRmeter^®^.

The data are collected online via the RéAC registry interface (http://www.registreac.org/), for which a direct data download functionality of the CPRmeter^®^ has been developed in collaboration with Laerdal. The data recorded by the CPRmeter® will therefore be retrieved from the memory after the end of the support upon return to the out-of-hospital resuscitation team’s base and will be transmitted securely—at the same time as those relating to the patient’s care—by Bluetooth connecting the CPRmeter^®^ to the RAC data collection server.

The patient, the family members, or the person of trust will be informed as soon as possible, and their consent (supplementary file) will be sought for the possible continuation of this research (according to article L1122-1-3) [27].

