#### Concomitant care and interventions

No concomitant medications, care, or intervention are prohibited as long as they do not interfere with the rhythm of CC relay or feedback device (CPRmeter^®^) use. The use of an automatic CC device set up before 5 min of CPR in the protocol is an exclusion criterion. If it is set up after 5 min, the collection of the CC data is restricted to those recorded before.

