#### Secondary outcomes

The secondary outcomes are as follows:
The depth of each CC (in millimeters), recorded continuously by the guidance system (average and percentage correct)The frequency of CC (in number of compressions per minute), recorded continuously by the guidance system (average and percentage correct)The release of the CC, corresponding to the residual force (in grams), recorded continuously by the guidance system (average and percentage correct)The subjective fatigability, assessed by the rescuers who performed CC using the Borg scale (average of the Borg rescuer scale values) [31]Time and length of care (in minutes and seconds) based on the following events: CA time, CC start time, the out-of-hospital resuscitation team’s resuscitation start time, and resuscitation end time (ROSC or death of the patient)The length (in minutes and seconds) of no-flow and low-flow: no-flow and low-flow times prior to the arrival of the out-of-hospital resuscitation team (declarative) and no-flow and low-flow times during resuscitation by the out-of-hospital resuscitation team (measured by the CC guidance device)The rate of return of spontaneous circulation (ROSC)The survival rate at hospital admissionThe value of NSE at admission and day 3 [28]The survival rate on day 1 and day 30 (or resuscitation output if earlier)Cerebral performance category score (CPC) at day 30 or intensive care discharge [29]

The study will be conducted within the framework of the French national network of the RéAC Cardiac Arrest Registry (http://www.registreac.org/).

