### Safety monitoring

A trio of independent experts not involved in the study (safety monitoring committee) will meet when 250 patients have been included to review the monitored data on ROSC and survival on day 0, day 1, and day 30 according to the randomized group. The investigator can request an extra meeting at any time in case of new data in the literature or if an event occurs in the study requiring the safety monitoring committee’s advice.

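### Use of an automated compression device stops NSE and CPC collection in patients who stay in the trial, and the text leaves unclear whether ROSC and survival stop too

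*Protocol article*

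**What the plan says.** The protocol article treats automated devices in three places.

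- **Exclusion criteria:** a device set up before 5 min of protocol CPR excludes the patient.
- **Concomitant care and interventions:** for later use, "If it is set up after 5 min, the collection of the CC data is restricted to those recorded before". This concerns compression data only.
- **Trial interventions:** the patient stays in the trial and the recorded compression data are kept, but collection of everything else is cut short: "but no more data (secondary criteria) are collected after the implementation of the automated CC device (no blood sampling or CPC score").

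Other sections plan the same outcomes with no exception for device patients. Follow-up under study plans NSE at admission and day 3. End of study has survival and CPC collected at day 30, at earlier intensive care discharge, or at death. Secondary outcomes lists ROSC, survival at admission, "The survival rate on day 1 and day 30" and "Cerebral performance category score (CPC) at day 30 or intensive care discharge". Data collection lists ROSC or death and survival at admission among the day-0 items. Under Safety monitoring, an independent committee meets at 250 patients to "review the monitored data on ROSC and survival on day 0, day 1, and day 30 according to the randomized group".

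The arm is drawn "during the transportation on the spot to know the randomization arm before the arrival at the place of the intervention", and the Blinding section states: "The study does not involve a blind setting for the healthcare providers".

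**The concern.** An included patient should contribute outcomes to the randomised arm whatever happens later. Here a later event ends collection. It always follows randomisation, and the people who decide on it know the arm.

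The event is unlikely to be unrelated to prognosis. Earlier device use leads to exclusion, so the rule reaches only patients whose resuscitation has already run for at least 5 min under protocol, while patients with early ROSC keep their full follow-up. A link with arm is possible as well. The Background reports from simulation that guidance delays fatigue-related loss of compression quality, and rescuer fatigue on the Borg scale is a secondary outcome. Both factors could change how often a team turns to a machine.

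At stake are NSE and CPC, the trial's marker of brain injury and its neurological outcome. If the sentence is taken literally, ROSC and survival, and with them the safety review by arm, are at stake too.

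**Working it through.** **Plan's own figures.** The plan gives no figure for device use. Its sample sizes reproduce but do not bear on this point: 2 × (1.960 + 1.282)² × 17²/5² = 242.9, so 243; with SD 36 and difference 15, 121.04, so 122. Only the total of 500 is used below, that is, about 250 per level of each factor.

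**Step 1: which outcomes stop.**

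| Outcome | Trial interventions, device patients | Other sections |
|---|---|---|
| NSE | stopped, named | planned, no exception |
| CPC | stopped, named | planned, no exception |
| ROSC, survival | not named; stopped only if the general wording is taken literally | planned, no exception; reviewed by the safety committee |
| CCF, CCS | kept up to the device | kept up to the device |

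The loss of NSE and CPC is explicit. The loss of ROSC and survival depends on the reading.

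**Step 2: how many patients.** Assume device use of 10% to 30%. Then 250 × 0.10 = 25 to 250 × 0.30 = 75 patients per factor level fall under the rule. No size can be put on the NSE bias, because the documents give neither the share of device patients admitted nor an NSE distribution.

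**Step 3: survival under the literal reading, with no true arm effect.** With true survival s, device share p and survival among device patients d, survival among patients with data is

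observed = (s − p × d) / (1 − p).

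Assumptions: s = 8.6%, inside the 6 to 11% given in the Background, and d = 3%.

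- p = 15%: (0.086 − 0.0045)/0.85 = 9.59%
- p = 25%: (0.086 − 0.0075)/0.75 = 10.47%; difference 0.88 points
- p = 10%: (0.086 − 0.003)/0.90 = 9.22%
- p = 30%: (0.086 − 0.009)/0.70 = 11.00%; difference 1.78 points
- p = 20% in both arms: (0.086 − 0.006)/0.80 = 10.0% in each; no false difference, but both are 1.4 points too high

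The false advantage goes to the arm with more device use. With s from 6% to 11% and d from zero to half of s, use of 10% v 30% gives 1.0 to 3.5 points. The false difference is zero if use is equal, or if device patients have the same prognosis as the rest.

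**Step 4: against sampling error.** At 10% v 30%, 225 and 175 patients remain. The standard error is √(0.0922 × 0.9078/225 + 0.11 × 0.89/175) = 3.05 points. At 15% v 25% it is 3.01 points. The false difference is thus about 0.3 to 0.6 of a standard error.

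**The case against.** The strongest reply concerns scope. A reader might infer that the rule definitely ends ROSC and survival collection, and so that the safety committee will see a truncated picture. The documents do not support this as a fact. The parenthesis names only blood samples and CPC, the Concomitant care section restricts only compression data, and four other sections keep ROSC or survival without exception. The narrow reading fits those sections better; the general wording fits the literal one. What stands is that the passages conflict. If survival is in fact collected, the Step 3 figures fall away.

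On the narrow reading the CPC loss may also be small. Table 1 scores death as 5, so a recorded death would fix the day-30 score and only device survivors would lack one. Under the Step 3 assumptions that is 250 × 0.10 × 0.03 = 0.75 to 250 × 0.30 × 0.03 = 2.25 patients per level, against 250 × 0.086 = 21.5 survivors. The protocol does not say that deaths would be scored this way.

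No section says why teams use a device or ties its use to fatigue or relay length, so unequal use is a possibility and not a finding. The Discussion concedes that the sample is probably too small for mortality and morbidity, and Step 4 agrees. Low precision does not justify a selective gap, however.

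Statistical analyses also plans multiple imputation for missing data in the pure intent-to-treat analysis. This helps in part, since initial rhythm, EtCO2 and low-flow duration are recorded and may explain some of the missingness. But standard imputation assumes missing at random, and for the stopped outcomes no device patient supplies a later value against which to check it. No remedy is stated for the exploratory secondary tests.

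**Conclusion.** The point holds for NSE and CPC: their collection stops, by explicit rule, after a post-randomisation decision by an unblinded team, so comparisons of these outcomes by randomised arm can be biased. That device use is related to prognosis is a strong inference from the 5-min rule; that it is related to arm is only possible. For ROSC and survival the finding is a contradiction to reconcile. The 0.9 to 1.8 points require the literal reading, unequal device use and the assumed survival rates together.

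A reader might also infer that the main results are compromised, or that every patient-outcome comparison is reduced to patients who needed no machine. Neither follows. CCF and CCS data up to the device are kept, the secondary tests are declared exploratory, and ROSC and survival may still be complete. This should be fixed, but it does not threaten the primary comparisons.

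**What to change.** Amend the sentence in Trial interventions so that only CPRmeter compression data stop at device placement. State that ROSC, survival to admission, day-1 and day-30 survival and CPC, and NSE through the existing sample circuit, are collected in every included patient and analysed by randomised arm whatever the device use. Bring Follow-up under study, End of study, Secondary outcomes, Data collection and Safety monitoring into line with it. Report device use by arm, and give the safety committee complete ROSC and survival data. For NSE and CPC values already missing, add a sensitivity analysis that does not assume missing at random.

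The cost is a short amendment, some extra data entry and some extra samples; the registry, eCRF and biobank circuit already exist. Trial status reports active recruitment since December 2019, so NSE samples already missed cannot be recovered. The change concerns data collection only and takes no view on when a device should be used.

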#### Follow-up under study

An NSE measurement will be performed upon the patient’s admission and on day 3 in accordance with the guidelines for the management of postanoxic coma states [28]. Blood samples will be collected into dry blood test tubes at the same time at admission and on day 3 to be sent to the University Hospital of Caen, Center for Biological Resources (CRB InnovaBIO, qualified NFS-96-900). The purpose is to perform a centralized NSE measurement (due to the large variability in the results from one laboratory to another). Samples will be sent within 30 min after sampling to the patient’s hospital center for biological resources (CRB), where they will be centrifuged and frozen at − 80 °C (within a time period of less than 2 h after sampling) and stored in a deep-freeze (− 80 °C) pending repatriation (every 2 months) of all the cryotubes (dry-ice shipping with temperature control) to the Center for Biological Resources (CRB InnovaBIO) of the University Hospital of Caen for analysis. The cryotubes (aliquots needed for dosing) will then be yielded and transferred from the CRB InnovaBIO, in dry ice, to the biochemistry department of the University Hospital of Caen for centralized measurement.

The survival and the CPC score (Table 1) [29] are collected on day 1 by the investigator in coordination with the patient’s unit and are sent to the data collection server.

**Table 1 Tab1:** Cerebral performance category (CPC) score

Score	Description
1	Good cerebral performance
2	Moderate cerebral disability
3	Severe cerebral disability
4	Coma or vegetative state
5	Death

#### End of study

At day 30 or upon discharge from the intensive care unit, if earlier, or upon the death of the patient, the investigating physician, in coordination with the last unit where the patient was, will collect the following data: survival, number of days of survival in case of death between day 1 and day 30 (or at the exit of resuscitation if earlier), and CPC score [29].

No long-term follow-up is planned.

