Values of the NSE performed upon the patient’s admission and on day 3 (in micrograms per liter) [28]Survival on day 1 and day 30 (or at the intensive care unit (ICU) discharge if earlier)Length of stay in the ICU (days)Neurological state assessment by the CPC and any sequelae on day 1 and at ICU discharge or on day 30 [29]

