### Schedule of data collection

Intervention assignment will be performed before starting the trial. If patients survive their CA, they will be followed up for 1 month after enrollment. The schedule of data collection is summarized in Table 2.

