### Statistical analyses

The main analysis population will be defined as all randomized patients for whom CPR has been engaged, according to a modified intent-to-treat principle. Randomized patients who do not fulfill the inclusion criteria, die, or have a ROSC at prehospital team arrival will be excluded from the main modified intent-to-treat principle analysis. We plan to conduct a pure intent-to-treat analysis in which these excluded patients and patients with missing data will have their outcome imputed by multiple imputation process. This analysis will test the effect of these exclusions on trial outcomes. The statistical analysis plan will follow the recommendations of the tests with a factorial plan described in the CONSORT statement [35], namely, (i) the verification of the absence of interaction between the 2 interventions tested (here on different criteria of judgment) and (ii) a separate analysis by type of multivariate intervention that will systematically include the effect of the untested intervention. Regarding the main criterion of judgment, the average percentage of CCF for comparison of A versus B and the average percentage of CCS for comparison C versus D, the two groups will be compared in terms of superiority of the 4-min group (B) and the guidance group (D) by a multivariate generalized linear regression model including the randomization group as an explanatory variable as well as the other intervention received as a covariable of the model and possibly the interaction of the 2 interventions if it is significant (Student’s test for independent series).

The other criterion (secondary outcomes) will be compared between the groups using the appropriate tests and in an exploratory manner. For example, the qualitative variables will be compared between the groups with the *χ*^2^ test, the quantitative variables by Student’s *t* test, and the survival by the log-rank test.

All confidence intervals of the parameters to be estimated will be established at 5% risk (95% confidence interval). No interim analysis will be performed for primary outcomes (CCF and CCS). The significance level is set at 0.05. The analysis will be performed in SAS software v9.4 (SAS Institute NC, Cary).

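### Day-30 survival and CPC are read at ICU discharge when that comes first, which conflicts with the stated one-month follow-up and leaves the log-rank test without defined data after ICU exit

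*Protocol article*

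**What the plan says.** Several sections of the protocol article allow the last reading to fall before day 30:

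- End of study: the final data are collected "At day 30 or upon discharge from the intensive care unit, if earlier, or upon the death of the patient". Survival time is recorded as the "number of days of survival in case of death between day 1 and day 30 (or at the exit of resuscitation if earlier". The section closes with "No long-term follow-up is planned".
- Secondary outcomes: "The survival rate on day 1 and day 30 (or resuscitation output if earlier" and "Cerebral performance category score (CPC) at day 30 or intensive care discharge".
- Data collection: "Survival on day 1 and day 30 (or at the intensive care unit (ICU) discharge if earlier", with CPC on day 1 and at ICU discharge or day 30.
- The Abstract and the secondary objectives under Study design and settings carry the same alternative.

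Other sections give a different end of follow-up:

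- Schedule of data collection: "If patients survive their CA, they will be followed up for 1 month after enrollment", with no ICU cut-off.
- Safety monitoring: the committee reviews survival on days 0, 1 and 30 by randomized group, again with no ICU cut-off.
- Data collection: the subheading above the late items refers to hospital discharge or day 30, although the items under it use ICU discharge.

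Statistical analyses treats all secondary outcomes as exploratory and gives, among its examples of tests, "the survival by the log-rank test".

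**The concern.** An outcome called day-30 survival should have a known status on day 30 for each patient. Here the reading moves forward to ICU exit, and the day of ICU exit is itself a consequence of the patient's course. A patient who leaves ICU early is read early; a patient who stays is read at day 30. The mix of reading days can differ between arms if the interventions change recovery, which is what the secondary objectives ask.

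A log-rank test needs, for each patient, a time and a reason why follow-up ended. For patients who leave ICU alive the collection rule supplies neither a day-30 status nor a later death date. At stake is whether the survival and neurological results can be read as day-30 results, both in the final report and in the data put before the safety committee. A statistical analysis plan can choose another test, but it cannot recover vital status or CPC that was not collected.

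**Working it through.** **Figures in the plan.** The article gives no sample size, event rate or precision for survival or CPC. Its sample sizes rest on CCF and CCS and reproduce with n = 2(1.960 + 1.282)² × SD²/difference² per group. For CCF, 21.01 × 17²/5² = 242.9, so 243. For CCS, 21.01 × 36²/15² = 121.0, and the exact t-based value is 122.0, so 122. Neither depends on the point made here.

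**What each rule records.** Take three kinds of survivor to admission.

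1. Still in ICU on day 30: the End of study rule and the one-month rule agree.
2. Leaves ICU alive, is alive on day 30, but CPC changes in between: survival agrees, but CPC is the ICU-exit value under one rule and the day-30 value under the other.
3. Leaves ICU alive and dies before day 30: recorded alive with CPC 1 to 4 under the End of study rule, and dead with CPC 5 (Table 1) under the one-month rule.

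The two rules therefore define different outcomes.

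**What the log-rank test could be given.** Patients in groups 2 and 3 can enter in two ways: (a) censored on the day of ICU exit, or (b) counted alive to day 30. The article does not choose. Way (a) assumes that patients who have left ICU have the same later hazard as those still there on that day. Way (b) assumes no deaths after ICU exit.

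**Hand illustration; all inputs assumed.** Of 100 admitted patients, 50 die by day 5, 40 leave ICU alive by day 12, and 6 of the remaining 10 die by day 30.

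- Way (b), alive at ICU exit or day 30: (40 + 4)/100 = 44%.
- Way (a), Kaplan-Meier with censoring at ICU exit: (1 − 50/100) × (1 − 6/10) = 20%.
- True day-30 survival if 0% of the 40 die after ICU exit: 44%. If 10% die (4 patients): (36 + 4)/100 = 40%.

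Here way (a) errs downward and way (b) is right or slightly high. The example shows only that the two ways differ.

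**Simulation; all inputs assumed.** 75% die on day 0. Of the 25% admitted, 60% die in ICU (exponential, mean 4 days) and 40% leave alive after a mean stay of 5, 8 or 12 days; 0 to 10% of those die by day 30.

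- True day-30 survival over all patients: about 9 to 10%.
- Way (b): about 10%. In a trial of 500 this corresponds to 500 × 0.25 × 0.40 = 50 patients leaving ICU alive, and 0 to 5 missed deaths.
- Way (a): about 0.2 to 0.4% (mean stay 5 days), 3.5 to 3.9% (8 days), 7.1% (12 days).

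**Comparison between arms under way (a).** Mortality is identical in both arms, there are no deaths after ICU exit, the test is at two-sided 5%, and 3,000 trials are simulated for each setting:

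| Setting | Mean ICU stay of survivors | Rejection, censored at ICU exit | Rejection, fixed day-30 status |
|---|---|---|---|
| All patients, 250 per arm | 8 vs 8 days | 4.8% | 5.1% |
| All patients, 250 per arm | 8 vs 5 days | 7.5% | 5.0% |
| Admitted only, 62 per arm | 8 vs 5 days | 12.3% | 5.3% |
| Admitted only, 62 per arm | 12 vs 5 days | 23.5% | 5.0% |

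The level of the survival curve can be badly wrong while the test keeps its 5% error. The error rises only when ICU stay differs between arms.

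**The case against.** A reader might infer that the plan censors patients at ICU discharge and that its survival comparison is therefore invalid. The article does not support that. It never mentions censoring or a Kaplan-Meier estimate, it offers the log-rank test only as an example, and the handling of discharged patients is detail that an analysis plan may settle. The secondary outcome is worded as a rate, and the same section assigns the chi-squared test to qualitative variables, so a comparison of proportions is already open to the sponsor. In the hand illustration with no late deaths, the documented outcome equals true day-30 survival.

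A reader might also take the inflated rejection rates as the expected error of this trial. They need a difference in ICU stay between arms that no section states. The largest also need the analysis to be confined to admitted patients, whereas the main population is all randomized patients in whom CPR was undertaken, where deaths on day 0 would dominate. The illustrations treat ICU exit as recovery; if some patients leave because care was stepped down, the bias could run the other way.

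The one-month sentence may be a loose summary of the maximum follow-up, and the schedule table cannot be read in the text at hand. The Discussion already concedes that the sample is probably too small for mortality and morbidity.

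All of this limits the size of the point. It does not remove the contradiction over when follow-up ends, or the fact that the collection rule leaves out deaths between ICU exit and day 30.

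**Conclusion.** The point holds as a contradiction over the timing of secondary outcomes and as a mismatch between the log-rank test and the data collected. Followed as written, survival and CPC are read at patient-specific, outcome-dependent times; deaths after ICU exit and before day 30 are missed; and some patients whose day-30 CPC is 5 are scored otherwise. This follows from the text alone.

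The effect on a comparison between arms has no size or direction that can be derived from the article. The figures in the working rest on assumed mortality, ICU stay and late deaths, and show only that the choice between censoring and counting patients alive can matter. The consequence is moderate at most: the outcomes are secondary and exploratory, and the CCF and CCS analyses and their sample sizes are untouched. It is worth correcting because status that was never collected cannot be supplied at the analysis stage.

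**What to change.** 1. Record vital status, and CPC where obtainable, at a fixed day 30 for every survivor wherever the patient is, from the hospital record, a telephone call or the RéAC registry. Record the date of any death up to day 30, including deaths after ICU exit.
2. Bring the Abstract, Study design and settings, End of study, Secondary outcomes and Data collection (including its subheading) into line with Schedule of data collection and Safety monitoring.
3. Compare day-30 survival as a proportion, with a risk difference and 95% confidence interval. Use the log-rank test only with administrative censoring at day 30.
4. If day-30 status cannot be collected, name the outcome alive at ICU discharge or day 30, analyse it as a proportion, and drop the log-rank test.

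The cost is a short status check for each patient who leaves ICU alive before day 30, a line in the eCRF, and a small amendment to a trial that is already recruiting. The article does not give the number of such patients. As an order of magnitude only, its background survival of 6 to 11% applied to 500 patients gives 500 × 0.06 = 30 to 500 × 0.11 = 55. No change to the sample size or the primary analyses is needed.
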